### Eligibility criteria {10}

In total, 50 patients will be included in the clinical trial if they meet the study criteria.

#### Inclusion criteria

Inpatient treatment at the Department of Psychiatry and Psychotherapy, University RegensburgMale and female patients in the age between 18 and 65 yearsVoluntary admission to the hospital independently from the trialDiagnosis of unipolar (ICD-10: F32, F33) or bipolar depression (ICD-10: F31.3–5)HAMD-21 score > 18Ability to conceive nature, meaning, and consequences of participation in the clinical trial and to understand and implement the explanations and instructions concerning the studyWritten informed consent after the trial has been comprehensively explainedIndication for pharmacological treatment independently from the trialWillingness to forgo the consumption of alcohol during participation in the studyWomen of Childbearing Potential (WOCBP) need a negative pregnancy test (serum β-hCG = serum human chorionic gonadotropin) at inclusion and need to be willing to use reliable contraception during the study (e.g., oral contraceptives, hormone-containing intrauterine coils, dermal or injectable contraceptives with long-term effects, tubal ligation). WOCBP are defined as women after menarche, which are not post-menopausal (at least 12 months no menstruation) and which did not undergo a documented hysterectomy, bilateral salpingectomy, or bilateral oophorectomy.Willingness to forgo to drive a car or to operate heavy machinesPatients with partners in a reproductive age must be willing to use appropriate contraceptives (Pearl-Index < 1%) for the duration of the studyDuring pregnancy of the partner the patients need to use a condom during sexual intercourse

#### Exclusion criteria

Diagnosis of a comorbid mental disorder like schizophrenia, addiction disorders according to ICD-10, or presence of another psychiatric main diagnosis in accordance with ICD-11 diagnosed using the Mini-International Neuropsychiatric Interview (M.I.N.I.) [32]Diagnosis of a severe somatic or neurological diseaseAcute suicidalityContraindications of the IMP: myasthenia, state of shock, severely impaired liver and/or renal functionContraindications against the implementation of functional Imaging (pacemaker, metal implants, tattoos in the head/neck area)Permanent treatment with 5alpha-reductase-inhibitors, pregabalin, or gabapentin over 2 weeks prior to participation in the studyHeart rate (HR) < 45 or > 110 bpmClinically relevant impairments in ECGBlood pressure: systolic < 90 or > 165 mm Hg, diastolic < 50 or > 95 mm HGBody temperature < 35 °C or > 37.5 °CBMI < 19 bzw. > 35Abnormal laboratory parameters of clinical relevance before study inclusion: Excess of thresholds: GPT, GOT and γ-GT above 20%, creatinine up to 0.2 mg/dL above age-adapted threshold; excess of the normal range more than twice as much of the upper standard or underrun of more than half of the lower standard for the other laboratory parameters (erythrocytes, leucocytes, thrombocytes, hemoglobin, hematocrit, MCH, MCHC, MCV, lymphocytes, monocytes, eosinophils, basophils, neutrophils, natrium, potassium, calcium, transferrin, ferritin, urea, uric acid, sober glucose, overall protein, triglycerides, cholesterol, HDL, LDL, C-reactive protein (CRP), bilirubin, TSH, free triiodthyronine (fT3), free thyroxine (fT4), Quick, PTT, HbA1c)Pregnancy or nursing periodAbuse of alcohol or drugs within the last 12 months before the inclusion screening diagnosed using the M.I.N.I.Dependence of alcohol or drugs in the medical history diagnosed using the M.I.N.I.Known allergy or hypersensitivity against etifoxine hydrochloride or one of the other components (talc, docusate sodium, sodium benzoate, preagglutinated starch, microcrystalline cellulose, Lactose Monohydrate, Magnesium stearate (Ph. Eur.), highly-dispersed silicon dioxide, titanium dioxide, indigotine, erythrosine)Galactose intolerance, lack of lactose, glucose-galactose malabsorptionCeliac disease, non-celiac-non-wheat allergic-wheat sensitivity (NCHS)Positive drug screening (amphetamines, cannabis, opiates, cocaine, ethyl glucuronide, ethanol, fentanyl, pregabalin, buprenorphine, methadone)Concurrent participation in another clinical trial according to AMG

### Who will take informed consent? {26a}

Before participation in the clinical trial, suitable patients are informed in detail about the clinical trial, its purpose, procedure, the investigational product, and possible risks both orally by a medical member or a psychologist of the trial team and in writing by the patient information leaflet. They will be notified about the voluntariness of participation in the study without any disadvantages for further clinical care in case of discontinuation. Afterwards, the patient is given at least 24 h to think about participating in the clinical trial. In case of agreement to join the trial patients will be asked to provide written consent.

### Additional consent provisions for collection and use of participant data and biological specimens {26b}

Not applicable, there are no ancillary studies planned. All information is provided within the patient information leaflet.

## Interventions

### Explanation for the choice of comparators {6b}

Patients in the control group will receive placebo capsules in addition to TAU. Since all study patients are allowed to be further treated with TAU, there are no ethical concerns of this control condition.

### Intervention description {11a}

During the treatment phase, the patients receive either 200 mg etifoxine/day (100–0–100 mg) or placebo treatment as an add-on to TAU for 14 days. During the treatment phase, the patients should take the medication orally (capsules) in two single doses (consisting of 2 capsules of 50 mg each) at 8:00 am and 6:00 pm.

The study medication will be administered to the patients by the nursing staff of the respective ward on all days at the two respective time points. The study medication is administered to the nursing staff by the medical members of the study group or the study assistants. The study medication may only be administered in accordance with the protocol guidelines.

### Criteria for discontinuing or modifying allocated interventions {11b}

Patients can end participation in the trial at any time without any consequences for further care. They must be withdrawn from the trial when judged necessary by the investigator, as for safety concerns, severe non-compliance, incorrect inclusion, or new development of an exclusion criterion. The data that have been collected up to that time point will be included in the analysis.

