### Procedure for unblinding if needed {17b}

Emergency envelopes for unblinding prepared by the pharmacy are kept locked in the research ward. In the event of an emergency, it is ensured that the trained ward staff has access to those envelopes at all times. In such a case, the sponsor must be informed on the next working day. A written justification will be submitted subsequently in this case. After unblinding, the clinical trial must be terminated for the respective patient.

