## Data collection and management

### Plans for assessment and collection of outcomes {18a}

The primary outcome parameter is ET50 estimated using the Hamilton Depression Scale (HAMD-21) scores collected on baseline day and on days 1, 2, 3, 4, 5, 6, 7, 8, 15, 22, and 29 of treatment. To guarantee good quality of the assessment, we have designated a fixed team of raters that were internally trained by experienced psychiatrists with a focus on high inter-rater consistency. Additionally, all ratings for one patient will consistently be performed by the same rater. For a description of all other outcome parameters see {12}.

A web-based, electronic Case Report Form (eCRF) within a validated database management system is used for the database-supported recording of study data. This system enables consistent data storage and quality control. Qualified entry personnel are given access to the eCRF by assigning personal login data. A medical investigator confirms timely with an electronic signature that the study data was entered into the database completely and correctly.

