### Plans to promote participant retention and complete follow-up {18b}

In case patients are discharged before the end of the study, there is the option to accomplish the measurements on days 22 and 29 in an outpatient setting. To at least compensate for the effort a little, patients receive monetary incentives of about 150 € as approved by the ethics committee for the completeness of data collection. Overall, the study team has a good track record in enrolling and following participants in previous trials.

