### Methods in analysis to handle protocol non-adherence and any statistical methods to handle missing data {20c}

The statistical analysis is performed using the intention-to-treat population. To check the robustness of the effects, further analysis will be performed on the per-protocol collective. We will perform a sensitivity analysis to examine the effect of missing data in primary and secondary outcome variables. Missing data will not be replaced within this clinical trial.

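### The withdrawal and unblinding rules do not separate the end of study medication from the end of HAMD-21 follow-up, which undermines the intention-to-treat analysis of ET50

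*Protocol article*

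**What the plan says.** Section {11b} of the protocol article concerns stopping or modifying the allocated intervention, but its rule is about leaving the trial: "They must be withdrawn from the trial when judged necessary by the investigator, as for safety concerns, severe non-compliance, incorrect inclusion". A newly developed exclusion criterion completes the list. The next sentence fixes which data are used: "The data that have been collected up to that time point will be included in the analysis". The article describes no route by which a patient stops study medication and stays in follow-up.

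Section {17b} has a second rule of the same kind, for emergency unblinding: "After unblinding, the clinical trial must be terminated for the respective patient".

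Section {20c} sets the analysis: "The statistical analysis is performed using the intention-to-treat population", with a per-protocol analysis as a robustness check. On missing scores it says "Missing data will not be replaced within this clinical trial" and also "We will perform a sensitivity analysis to examine the effect of missing data in primary and secondary outcome variables".

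Section {18a} builds the primary outcome, ET50, from HAMD-21 "scores collected on baseline day and on days 1, 2, 3, 4, 5, 6, 7, 8, 15, 22, and 29 of treatment". Section {20a} fits a two-parameter Emax curve (Emax and ET50) to each patient and compares the group means by t-test. For patients discharged early, {18b} says "there is the option to accomplish the measurements on days 22 and 29 in an outpatient setting".

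**The concern.** Severe non-compliance and incorrect inclusion are departures that an intention-to-treat analysis is meant to look past. If such patients leave the trial altogether, their later outcomes are never measured. The intention-to-treat data then drift towards the per-protocol data, and the per-protocol analysis says less as a robustness check.

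Some triggers can follow from the outcome itself. Acute suicidality is an exclusion criterion, and suicidality is rated on days 8, 15, 22 and 29. Withdrawal for a newly developed exclusion criterion can therefore depend on how the depression is going, and its rate could differ between arms.

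The endpoint makes this worse. ET50 depends on where the curve levels off, so it needs late ratings. No ratings are scheduled on days 9 to 14, so a patient withdrawn in that window has nothing after day 8. An analysis plan can choose how to treat a truncated curve, but it cannot recover ratings that were not taken.

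**Working it through.** **The plan's own allowance.** {14} needs 20 patients per group and assumes 10–20% drop-out. 20 / (1 − 0.20) = 25 per group, 50 in total, which is the stated figure. At 10% the result is 20 / 0.90 = 22.2, or 23 per group. Of 50 randomised, 10–20% is 5 to 10 patients. The sample size thus already allows for lost patients; the question is what their loss does to the endpoint.

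**Inputs from {14}.** Emax = 0.586, ET50 = 4.224 days, s = 2.6 points. Visits are from {18a}.

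**Assumptions not in the document.** Baseline HAMD-21 B of 22, 25 or 28; s taken as independent noise at each visit; baseline known without error, except where stated.

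**Model.** y(t) = B × [1 − Emax × t / (ET50 + t)].

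**Standard error of one patient's ET50.** The derivatives at each visit are a = −B·t / (ET50 + t) for Emax and b = B·Emax·t / (ET50 + t)² for ET50. Then Var(ET50) = s² × Σa² / (Σa²·Σb² − (Σab)²).

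Worked case, B = 25, visits to day 8: Σa² = 1252.76, Σb² = 5.0464, Σab = −77.453. The denominator is 1252.76 × 5.0464 − 77.453² ≈ 322.9. Var = 6.76 × 1252.76 / 322.9 ≈ 26.2, so SE ≈ 5.1 days.

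| Last rating | SE at B = 25 (days) | Range, B = 28 to 22 (days) |
|---|---|---|
| Day 4 | 11.9 | 10.7–13.6 |
| Day 8 | 5.1 | 4.6–5.8 |
| Day 15 | 3.5 | 3.1–4.0 |
| Day 29 | 2.3 | 2.1–2.6 |

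The true ET50 in this illustration is 4.2 days. Day 29 is the full schedule in {18a}. Day 15 is shown because the primary objective in {7} runs to that day.

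**Simulated per-patient fits (Nelder-Mead, B = 25).** Share with a fitted ET50 beyond 29 days, the end of follow-up:

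| Last rating | Baseline known | Observed noisy baseline used |
|---|---|---|
| Day 4 | about 30% | about 33% |
| Day 8 | about 12% | about 23% |
| Day 15 | about 3% | about 8% |

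These shares move by a few percentage points between runs. With data to day 29 and a known baseline, essentially no fit goes beyond 29 days. Some fits to very short curves run off to extremely large values, and one such value can dominate a group mean. With at most one post-baseline score, the two parameters cannot both be estimated.

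**The case against.** A reader might infer that {11b} contradicts {20c}. The documents do not support that. Withdrawn patients' data up to withdrawal stay in the analysis, no randomised patient is said to be excluded, and a sensitivity analysis for missing data is planned. The statements can stand together; what suffers is the completeness of the data.

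A reader might also infer automatic withdrawal on each trigger. The rule rests on the investigator's judgement and gives its triggers as reasons. Nor does any sentence say outright that ratings stop; that follows from leaving the trial and from the limit on which data are used. The article condenses a fuller protocol, which may say more. Still, what the article does state is withdrawal from the trial, and {17b} says much the same.

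Further points stand. Section {18b} is about patients discharged early, not patients withdrawn, so it is weak evidence here. Ratings after emergency unblinding are open to bias, so continuing them has a cost. Even complete data to day 15 give a standard error of about 3.5 days on a true value of 4.2, so much of the instability comes from the per-patient fit and not from withdrawal. How extreme or inestimable fits are handled may be settled in the analysis plan.

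**Conclusion.** The point holds as a weakness in follow-up. As written, {11b} and {17b} end outcome collection together with treatment, for reasons that can depend on adherence or outcome, while {20c} needs those scores and does not replace them. Under the stated assumptions, stopping at day 4 rather than day 15 raises the standard error of a patient's ET50 by a factor of about 3.4 (11.9 / 3.5), and stopping at day 8 by about 1.5 (5.1 / 3.5). This direction holds across baselines of 22 to 28; the shares of extreme fits also depend on whether the baseline is treated as known.

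It would be wrong to read 5 to 10 as the number lost through these rules. That is the total drop-out allowance and therefore an upper bound. It also covers patients who withdraw consent, whom no rule change recovers, and the Discussion reports no drop-outs in earlier etifoxine trials at the site. The document gives no basis for a direction or size of bias in the treatment comparison.

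**What to change.** Leave the medication-stopping rules as they are. In {11b}, state that the end of study medication is not the end of follow-up, and that scheduled HAMD-21 ratings continue to days 15, 22 and 29 for every randomised patient who does not withdraw consent. In {17b}, continue the ratings too, but flag those made after unblinding and examine their influence in a sensitivity analysis. Optionally, extend the outpatient option in {18b} to the day 15 HAMD-21 rating.

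The cost is an amendment and a few extra ratings by the rater already assigned to the patient. The intention-to-treat data will then include some off-treatment or unblinded scores, which should be identifiable. At the reported status date 15 of 50 patients had been included, so an amendment at that point could have covered most of the sample.

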### Strategies to improve adherence to interventions {11c}

Some of the measurements taken in this trial can be integrated into the clinical routine. Both, the incidence of serious adverse reactions to the investigational product and risks of harm by any of the measurements are low. In the first week of treatment, patients will have daily contact to one of the investigators. Also afterwards, there will be regular communication with the patients to improve compliance and minimize the risk of drop-outs.

### Relevant concomitant care permitted or prohibited during the trial {11d}

The additional administration of benzodiazepines (lorazepam up to 3 mg/day) should only take place in cases of clinical necessity. On the days before the fMRI scans, the concomitant medication should not be administered if possible.

### Provisions for post-trial care {30}

After completion of the clinical trial patients continue to be treated by the ward doctors, provided they still require inpatient treatment. Any harm that occurs during the course of participation will be covered by trial insurance.

### Outcomes {12}

#### Self-ratings

To assess the course of the clinical symptoms and respective effects of the treatment several psychometric instruments will be applied. Using the Patient Health Questionnaire 9 (PHQ-9) [33] and the Beck-Depression-Inventory (BDI) [34] depressive symptoms will be rated. Visual analog scales (VAS) [35] will be used to check for further symptoms associated to depression (depressive mood, anxiousness, lack of drive, and somatic issues) as well as an estimation of the general state. Using the Stanford Sleepiness Scale (SSS) [36], we will check for daily sleepiness. Possible symptoms related to withdrawal or drug dependence will be assessed using the Benzodiazepine Hypnotics Withdrawal Symptom Scale (BHWSS) [37] and the Benzodiazepine Dependence Self-Report Questionnaire (BENDEP-SRQ) [38].

#### External ratings

All external ratings will be conducted by experienced members of the trial team (physicians, psychologists). The severity of depressive symptoms will be assessed by the Hamilton-Depression-Scale (HAMD-21) as well as the Montgomery–Åsberg Depression Rating Scale (MADRS) [39]. Anxiety symptoms will be assessed using the Hamilton-Anxiety-Scale (HAMA) [40]. Additionally, we will determine the risk of suicidality with the Columbia Suicide Severity Rating Scale (C-SSRS) [41].

#### Functional magnetic resonance imaging

We will perform (f)MRI measurements at a Siemens 3 Tesla MRI scanner. Each session will consist of one resting-state measurement and two task-based scans.

##### Resting-state measurements

Using task-free resting-state fMRI, we plan to identify so-called functional networks, which reflect the integration of information processing in different brain regions underlying complex behavior [42]. Therefore, patients are asked to lie still in the MRI scanner for 22 min, close their eyes, and not to fall asleep.

##### Task 1: cognitive and neuronal representations

This task consists of a behavioral and an imaging part. In the behavioral part, patients are asked to arrange emotional terms on a computer screen in a 2-dimensional space using “drag-and-drop.” In this so-called “ARENA method,” the distances between the terms reflect their dissimilarity [43]. In the imaging part, which was adapted from Thornton et al. [44], patients are presented with two different statements (e.g., “I am happy,” “I am content”) of the same emotion class, e.g., “Joy,” together with the class name above the statements. Patients are asked to press a button to indicate which of these statements better represents the emotional category for them. RSA can be used to search for brain regions that show neuronal distance patterns similar to the behavioral distance matrices.

##### Task 2: face-name-associations

In this task, patients are first presented with two pairs of faces and written names in an event-based paradigm with the instruction to learn these two associations. Afterwards, the previously shown face-name pairs (old) are presented alternately with new face-name pairs (new). The aim for the patients is to learn as many face-name pairs as possible for a subsequent memory test. This task allows us to measure the hypothesized indirect effect of etifoxine on the GABAergic system. An attenuation of the BOLD response to novel stimuli was shown after acute administration of the benzodiazepine lorazepam [23]. In addition to the design of Sperling et al., a measurement is made during the acquisition phase, which makes it possible to check whether the administration of etifoxine leads to a flattening of the so-called repetition suppression [4] compared to placebo and whether this results in reduced performance in the subsequent memory test.

#### Cambridge Neuropsychological Test Automated Battery (CANTAB)

The Cambridge Neuropsychological Test Automated Battery (CANTAB, Cambridge Cognition Lt., Cambridge, UK) is a computer-based procedure that contains a total of 25 tests to record cognitive abilities. These can be used to assess various axes of cognition, such as sustained attention, the ability to recognize visual correspondences and basic emotions, and memory performance. The total completion time is approximately 40 min. The following subtests are used in this clinical trial:Rapid Visual Information Processing (7 min): measurement of sustained attentionOne Touch Stockings of Cambridge (10 min): assessment of executive function via the subdomains of spatial planning and working memorySpatial Working Memory (4 min): assessment of executive function and strategic approach/working memoryDelayed Match to Sample (7 min): testing the ability to recognize visual matches and short-term recognition of visual stimuliEmotion Recognition Task (6–10 min): assessment of the ability to recognize the 6 different basic emotions using morphed facial expressions on a continuum

#### Blood samples

During the course of the clinical trial, venous blood is taken from the patients on the one hand to screen for safety parameters (screening or safety blood) on the other to test secondary endpoints (study blood). The following blood parameters are collected in each case:

##### Screening or safety blood (sober)

Erythrocytes, leukocytes, thrombocytes, hemoglobin, hematocrit, MCH, MCHC, MCV, lymphocytes, monocytes, eosinophils, basophils, neutrophils, sodium, potassium, calcium, transferrin, ferritin, creatinine, urea, uric acid, fasting glucose, total protein, bilirubin, triglycerides, cholesterol, HDL, LDL, GPT, GOT, γ-GT, C-reactive protein (CRP), TSH, free triiodothyronine (fT3), free thyroxine (fT4).

Additionally, during screening: Quick, PTT, HbA1c; for WOCBP: β-HCG.

